## Abstract

**Background:**

Non-cystic fibrosis bronchiectasis is characterised by sputum production, exercise limitation and recurrent infections. Although pulmonary rehabilitation is advocated for this patient group, its effects are unclear. The aims of this study are to determine the short and long term effects of pulmonary rehabilitation on exercise capacity, cough, quality of life and the incidence of acute pulmonary exacerbations.

**Methods/Design:**

This randomised controlled trial aims to recruit 64 patients with bronchiectasis from three tertiary institutions. Participants will be randomly allocated to the intervention group (supervised, twice weekly exercise training with regular review of airway clearance therapy) or a control group (twice weekly telephone support). Measurements will be taken at baseline, immediately following the intervention and at six and 12 months following the intervention period by a blinded assessor. Exercise capacity will be measured using the incremental shuttle walk test and the six-minute walk test. Quality of life and health status will be measured using the Chronic Respiratory Questionnaire, Leicester Cough Questionnaire, Assessment of Quality of Life Questionnaire and the Hospital Anxiety and Depression Scale. The rate of hospitalisation will be captured as well as the incidence of acute pulmonary exacerbations using a daily symptom diary.

**Discussion:**

Results from this study will help to determine the efficacy of supervised twice-weekly pulmonary rehabilitation upon exercise capacity and quality of life in patients with bronchiectasis and will contribute to clinical practice guidelines for physiotherapists in the management of this population.

**Trial registration:**

This study protocol is registered with ClinicalTrials.gov (NCT00885521).

## Background

Bronchiectasis not related to cystic fibrosis (non-CF bronchiectasis) is characterised by permanent dilatation of the airways arising from bronchial inflammation and infection [1]. Predominant symptoms include cough with sputum production, dyspnoea and fatigue [2-4]. This clinical profile contributes to progressive deconditioning, which gives rise to reduced exercise tolerance and diminished health-related quality of life (HRQoL) [2,5,6]. Patients with bronchiectasis suffer from recurrent acute exacerbations, which may require hospitalisation [7,8]. This clinical course of bronchiectasis imposes considerable economic cost to the healthcare system [9,10]. More importantly, the incidence of pulmonary exacerbations is a prognostic predictor in bronchiectasis, with progressive airway damage and decline in respiratory function greater in those experiencing a higher incidence of acute exacerbations [11].

Medical intervention has limited impact on disease progression or exercise capacity and evidence regarding the cost effectiveness of any therapeutic approach in bronchiectasis is scant [1]. Exercise and self management training, as a component of a pulmonary rehabilitation (PR) program is a well-established and effective intervention for patients with chronic obstructive pulmonary disease (COPD), leading to reductions in the incidence of acute exacerbations and reduced health care utilisation as well as improvements in exercise tolerance and HRQoL [12-16]. Although international guidelines for PR recommend the inclusion of patients with bronchiectasis within existing programs [12], there is a lack of evidence supporting this practice [17]. One study has compared exercise training with or without inspiratory muscle training to standard medical care [18]. While significant short-term improvement in exercise capacity was demonstrated, benefits in HRQoL were only achieved with a combination of whole body exercise and inspiratory muscle training. The clinical significance of these findings is unclear, as the administered intervention differed from current recommendations for PR [12,19]. Although inspiratory muscle training was applied as a form of airway clearance therapy (ACT) in this study [18], no beneficial effects on ease of sputum expectoration were demonstrated. The long term benefits of PR which incorporates exercise training and self management in ACT compared to standard medical care, on exercise capacity and dimensions of HRQoL, including fatigue, anxiety and depression remains unknown. Furthermore, evaluation of the efficacy of such an intervention on the incidence of acute pulmonary exacerbations of bronchiectasis may provide evidence to determine best practice guidelines in this patient population.

The primary aims of this study are to (1) determine the short and long term effects of an eight-week PR program consisting of supervised exercise training and self management education in ACT compared to standard care on exercise capacity and HRQoL; and (2) establish the effect of this intervention on the incidence of acute exacerbations over a 12 month period in patients with bronchiectasis. We hypothesise that patients who complete PR will have a higher exercise capacity and HRQoL compared to standard care and that these benefits will be sustained for up to six months. PR will also reduce the incidence of pulmonary exacerbations over 12 months.

## Methods/Design

### Study design

This multi-centre, randomised controlled trial (RCT) will be conducted at Alfred Health and Austin Health, Melbourne, the Lung Institute of Western Australia and Sir Charles Gairdner Hospital, Perth, Australia.

### Participants

#### Inclusion/exclusion criteria

To be eligible for enrolment, participants must be aged ≥ 18 years and have a diagnosis of bronchiectasis that is not attributable to CF, confirmed radiologically on high resolution computed tomography. They must be clinically stable, with no evidence of an exacerbation of bronchiectasis or changes in medical therapy in the previous four weeks [7]. Other inclusion criteria comprise of exertional dyspnoea (Modified Medical Research Council (MMRC) score ≥ 1) [20] and a history of at least two exacerbations per year over the past two years.

Participants will be excluded if they have 1) smoking history ≥ 10 pack years or physician diagnosis of COPD [21]; 2) a clinical diagnosis of asthma [22]; 3) interstitial lung disease (clinical/radiological diagnosis); 4) medical conditions which could place the individual at risk during exercise testing or training (eg. unstable cardiovascular disease) or conditions that may restrict the participant's ability to exercise (eg. severe orthopaedic or neurologic impairments; 5) participation in a PR program within the last 12 months.

#### Sample size

To detect a true difference in the primary outcome measures of maximal exercise capacity and HRQoL, a total of 36 subjects (18 per group) will be required. This is based on the 80% probability of detecting statistically and clinically significant differences in maximal exercise capacity (incremental shuttle walk test [ISWT]) [18] and HRQoL (Chronic Respiratory Questionnaire [CRQ] total score), according to pilot data from 33 patients with bronchiectasis who completed PR at Alfred Health. To detect a true difference for the secondary outcome measure of the incidence of acute exacerbations, a total of 64 subjects will be required. This is based on the 80% probability of detecting a true difference in the number of exacerbations between groups is 1.0 exacerbation, with a SD of 1.4 exacerbations [11].

#### Recruitment and randomisation

The flow of participants through the study will reflect the recommendations from the Consolidated Standards of Reporting Trials statement [23] and is outlined in Figure 1. Participants will receive written and verbal information explaining the study and written consent will be obtained from all participants. The Human Research Ethics Committee of Alfred Health, Austin Health and Sir Charles Gairdner Hospital approved the study and the protocol is registered with ClinicalTrials.gov (NCT00885521).

**Figure 1 F1:**
[figure not shown]
**Flow of patients through the study**.

Participants will be screened from the Lung Institute of Western Australia (LIWA) database of individuals with bronchiectasis or during outpatient clinic visits to Physiotherapy or Respiratory Medicine at Alfred Health, Austin Health and Sir Charles Gairdner Hospital, by the study investigators. If eligible, the study investigators will approach the participant to explain the study and gain written, informed consent. It will be explained that they may withdraw from the study at any time. Within strata, participants will be randomly assigned to receive either standard care alone or PR. The strata are sputum quantity (small volume: up to one tablespoon per day, large volume: > one tablespoon per day) and the site of randomisation. The randomisation will be completed by the creation of a random numbers table and individual group assignment will be kept in sealed opaque envelopes. Following baseline assessments, a physiotherapist will collect the appropriate envelope after confirming sputum quantity. A computer-generated randomised order for performing the field walking tests for each participant will be determined before baseline measures and adhered to throughout the study.

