### Outcome measures

All outcome measures will be recorded at baseline, immediately following the intervention period (nine weeks) and at six and 12 months post completion of the intervention (Figure 1). Baseline data collection will include age, gender, body mass index, usual ACT if previously prescribed and MMRC scale for dyspnoea [20]. The number of acute pulmonary exacerbations per year in the previous two years will also be collated. An exacerbation will be defined as an increase in clinical signs and symptoms requiring alteration of medication, including antibiotic therapy according to participant recall and medical record review.

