### Statistical analysis

Data will be entered into SPSS (version 17.0; SPSS Inc; Chi) for analysis. Descriptive statistics will be used to examine the distribution and data that are not normally distributed will be transformed or analysed using non-parametric tests. Analyses will be conducted using an intention to treat principle. Repeated measures analysis of variance with planned comparison will be used to compare all continuous variables that are normally distributed. Significant results will be analysed using post hoc tests. Categorical variables will be analysed using the chi square statistic. Relationships between outcome variables will be analysed using correlation coefficients. The alpha level for all statistical analyses will be set at 0.05.

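### The stated repeated measures ANOVA carries neither the randomisation strata nor a baseline covariate and does not name the treatment comparison, so precision is given up

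*Protocol article*

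**What the plan says.** Under Recruitment and randomisation, the protocol article allocates within strata: "The strata are sputum quantity (small volume: up to one tablespoon per day, large volume: > one tablespoon per day) and the site of randomisation". On the allocation list it says: "The randomisation will be completed by the creation of a random numbers table and individual group assignment will be kept in sealed opaque envelopes". No blocking is described.

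Under Outcome measures: "All outcome measures will be recorded at baseline, immediately following the intervention period (nine weeks) and at six and 12 months". Exacerbations are different. Their only baseline is historical: "The number of acute pulmonary exacerbations per year in the previous two years will also be collated". That count comes from recall and medical records, whereas exacerbations during the trial come from a daily diary with a symptom-based definition.

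Under Statistical analysis: "Repeated measures analysis of variance with planned comparison will be used to compare all continuous variables that are normally distributed". The next sentence reads: "Significant results will be analysed using post hoc tests". For categorical data: "Categorical variables will be analysed using the chi square statistic". The section mentions neither site nor sputum stratum and no baseline covariate. It does not say whether baseline is one of the repeated levels, or which comparison is the test of treatment.

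**The concern.** The design collects information that the stated analysis does not use fully. Stratifying by site and sputum volume implies that these are expected to be prognostic, and a baseline value is usually the strongest predictor of a follow-up value. A model without them leaves explainable variation in the error term.

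The unnamed treatment comparison adds to this. If baseline is one of four repeated levels, a group main effect averages in a time at which no treatment effect can exist. A group-by-time test spreads the effect over three degrees of freedom. Planned comparisons and post hoc tests of significant results both appear, and the text does not say whether the differences at individual times depend on a significant overall test.

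At stake is power in a trial of 64 patients, most of all for exacerbations, the outcome that sets that number.

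**Working it through.** **The plan's own figure.** For exacerbations, a difference of 1.0 with SD 1.4 gives d = 1.0/1.4 = 0.714. A two-sided two-sample t-test at 0.05 with 80% power needs 31.76, so 32 per group and 64 in total, as stated. Power at 32 per group is 80.3%, so there is no slack. The 36 for the primary outcomes cannot be rebuilt, because no difference or SD is given; 18 per group implies d of about 0.96.

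**Assumptions.** The article gives neither the baseline-to-follow-up correlation (rho) nor the share of outcome variance explained by the strata (R²). Both are varied below. Correlation is taken as equal between all times, with n = 32 per group and unit SD.

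**Baseline, single follow-up time.** The change-score variance is 2(1−rho) and the baseline-adjusted (ANCOVA) variance is 1−rho². The ratio is (1−rho²)/[2(1−rho)] = (1+rho)/2. At a true difference of 0.5 SD:

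| rho | ratio | change-score power | ANCOVA power |
|---|---|---|---|
| 0.5 | 0.75 | 0.504 | 0.623 |
| 0.6 | 0.80 | 0.595 | 0.692 |
| 0.7 | 0.85 | 0.720 | 0.787 |
| 0.8 | 0.90 | 0.876 | 0.907 |

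**Choice of comparison.** Take rho 0.6 and assumed effects of 0, 0.5, 0.25 and 0 SD at baseline, nine weeks, six months and 12 months.
- Group main effect: the mean effect is 0.75/4 = 0.1875. The variance of a four-time mean is (1+3×0.6)/4 = 0.70. The standard error is √(2×0.70/32) = 0.209, the ratio is 0.90, and power is about 14%.
- Group-by-time: the squared deviations of the four effects from their mean sum to 0.1719. The noncentrality is 16×0.1719/0.4 = 6.88 on 3 and 186 degrees of freedom, and power is about 57%.
- Nine-week ANCOVA: the standard error is √(2×0.64/32) = 0.20, the ratio is 2.5, and power is about 69%.

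If the effect is instead held to six months (0, 0.5, 0.5, 0), the group-by-time noncentrality is 16×0.25/0.4 = 10 and power is about 75%, above the 69% for the nine-week contrast alone. The group main effect has a mean effect of 0.25 and power of about 22%. At effects of 0, 0.96, 0.48 and 0, group-by-time and ANCOVA both exceed 99%.

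**Strata.** This is a simulated comparison of one follow-up value without a baseline term: 64 patients, six strata (three sites by two sputum levels), d = 0.714, 10,000 null and 4,000 alternative runs. The adjusted analysis fits all six strata.

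| R² | blocks of 4: unadjusted type I error | blocks of 4: power, unadjusted / adjusted | no blocks: power, unadjusted / adjusted |
|---|---|---|---|
| 0 | 0.050 | 0.81 / 0.80 | 0.79 / 0.75 |
| 0.1 | 0.039 | 0.81 / 0.84 | 0.80 / 0.81 |
| 0.2 | 0.028 | 0.83 / 0.89 | 0.80 / 0.84 |
| 0.3 | 0.020 | 0.83 / 0.91 | 0.80 / 0.90 |

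Without blocks, unadjusted type I error stays at 0.046 to 0.053. With balanced strata, R² 0.2, rho 0.6 and stratum effects constant over time, a change-score test has type I error of about 0.05 (0.049 and 0.054 in two simulations), because stable stratum effects cancel. A follow-up-only test in the same setting gives 0.028 to 0.029.

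**The case against.** The strongest reply is that this is a condensed article with one analysis paragraph, and that covariates may be listed in an analysis plan not shown. Nothing in the text says the analysis is unadjusted. That limits the weight of the point. It does not remove it, because the article commits to a specific method for every normally distributed continuous outcome, and a better one is available at almost no cost.

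A reader might infer that baseline is ignored altogether. The text does not support that: a group-by-time comparison that includes baseline is in effect a change-score analysis, which is valid in a randomised trial. The criticism is of efficiency and of an unnamed contrast. Planned comparisons are also already mentioned, so the 14% applies only if the four-time main effect is the treatment test, which the article never says.

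A reader might also infer that ignoring the strata makes the error rates wrong. That does not hold for the design as described. No blocking is stated, and without it type I error is nominal. Under balanced allocation the distortion is conservative and affects between-subject comparisons; a within-subject comparison stays near 5%.

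Finally, the gain depends on the scenario. The article's own hypothesis is that benefit lasts up to six months, and in that pattern the group-by-time test does well. At the effect implied by 36 patients, with 64 recruited, the loss for the primary outcomes is negligible. All of this stands.

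**Conclusion.** The point holds as a loss of precision and an unnamed treatment comparison. There is no bias, no inflated false-positive rate and no contradiction in the text. At an assumed effect of 0.5 SD, baseline adjustment adds about 3 to 12 percentage points of power over a change score as rho falls from 0.8 to 0.5. Adjusting for strata adds about 1 to 10 points without blocking, and about 3 to 8 with blocks of four, for assumed R² of 0.1 to 0.3 in a follow-up-only comparison. These two gains should not be added together, because baseline and strata may explain the same variation. A group main effect over all four times would be a poor treatment test: about 14% to 22% power in the two fading patterns examined.

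Every size here rests on assumed rho, R² and effect pattern. The practical importance is greatest for exacerbations, where 64 patients give 80.3% power, and small for the primary outcomes if the true effect is near 0.96 SD.

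**What to change.** For each continuous outcome, model the nine-week, six-month and 12-month values together, with the baseline value, site and sputum stratum as main-effect covariates, and take baseline out of the set of repeated outcomes. Name the between-group differences at the three follow-up times as the planned comparisons, and state that they do not depend on a significant overall test.

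For exacerbations, adjust the 12-month comparison for site, sputum stratum and the exacerbation rate over the previous two years. That rate is only a proxy baseline, since it is recorded differently from the diary events.

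The cost is a sentence or two of text and about four degrees of freedom: two for three sites, one for sputum and one for baseline. It is five if the Lung Institute of Western Australia, listed separately under Study design, counts as a fourth site. If the covariates prove not to be prognostic there is a small power loss. The simulation at R² = 0 without blocking shows 0.79 falling to 0.75 with all six strata fitted; main effects alone use fewer terms.

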### Intervention

#### Standard care group

These participants will receive instruction and review of ACT provided by a senior physiotherapist. This process is consistent with current clinical management at each recruitment site. Each participant will be provided with written information about bronchiectasis [24] and education regarding self-management of the condition. Participants who have not been previously instructed in any ACT will be taught the active cycle of breathing technique [25]. Participants previously instructed in other forms of ACT (eg. positive expiratory pressure therapy, oscillating positive expiratory pressure therapy) will have their technique reviewed, corrected if necessary and encouraged to continue with this corrected technique for the study duration. Instructions in ACT will be given during the baseline assessment. These participants will not receive any supervised exercise training but will be informed at the baseline assessment that accumulating 30 minutes of moderate intensity physical activity on most days of the week is the standard recommendation for health benefits. During the eight-week intervention period, participants will be contacted by telephone twice weekly. The purpose of these calls is to answer any questions the participant may have regarding performance of their ACT and to provide support and general health advice using a standardised script. This is an accepted strategy to control for clinician contact in trials involving disabled patients with chronic lung disease and has been previously used in patients with interstitial lung disease [26]. No specific discussion related to physical activity will be undertaken during these telephone calls.

#### Pulmonary rehabilitation group

Participants randomised to the PR group will receive exercise training and regular instruction in self-management of ACT. No additional formal education sessions will be included. Participants will receive the identical instruction in ACT as described for the standard care group. Self management strategies to encourage regular adherence with ACT will also be implemented. Once a week at the conclusion of a PR session, participants will record their daily sputum volume on a 100 mm visual analogue scale and have their ACT reviewed by a senior physiotherapist. This will include observation of the participant's technique with correction where necessary and discussion of any concerns or problems the participant is experiencing with the self-management program.

The eight-week exercise training program will comprise of two supervised exercise classes at the institutions each week with a home walking program on two additional days per week. The exercise program will follow recent guidelines for exercise prescription in chronic lung disease [19]. This will comprise of 30 minutes of endurance exercise at each supervised session, including walking and cycling. Initial walking intensity will be prescribed at 75% of the maximal work rate achieved on the ISWT while cycling intensity will be based on data obtained from the 6-minute walk test (6MWT) [27]. For participants unable to tolerate continuous exercise, interval training will be used. Participants will also complete a circuit of upper limb endurance exercises and functional strength training for the lower limbs. An experienced physiotherapist will monitor participants during the exercise classes and progress the exercise within symptom tolerance of dyspnoea and fatigue based on the 0 to 10 Borg scale [28]. Supplemental oxygen will be provided during training if necessary to achieve an oxygen saturation >85% [19]. Following the establishment of a safe, supervised exercise regimen, a home exercise program will be prescribed, with participants encouraged to walk for 30 minutes at an intensity similar to that achieved in the supervised sessions. Participants will record these walking sessions in a home exercise diary. Attendance at 12 out of 16 supervised sessions will be considered completion of the exercise intervention. At the completion of the intervention period, participants will be instructed to continue with their home exercise program three to five times per week and to record these sessions in their exercise diary.

